#### Exclusion criteria

Have an untreated clinical condition (e.g., anemia or hypothyroidism) or comorbid condition (e.g., chronic fatigue syndrome) that pre-dates PARP inhibitor use and could explain fatigue.Have a history of chronic untreated trauma (unrelated to their cancer), psychiatric hospitalization or suicide attempt(s) in the past 5 years, or are currently at high risk for suicidality. Adults excluded for any of these reasons will be referred to broader or more intensive supportive resources.Patients with cognitive conditions (e.g., dementia) determined by their treating oncologist or Site PI, such that they could not provide informed consent or complete the study procedures.

### Participant recruitment and consent

As ovarian cancer is a relatively rare form of cancer, participants will be recruited from multiple sites, including the Dana-Farber Cancer Institute (DFCI), Massachusetts General Cancer Center, and the Cancer Center at Beth Israel Deaconess Medical Center (BIDMC) in Massachusetts; University of Colorado Cancer Center in Colorado; and Duke Cancer Center in North Carolina. In addition, to better understand the intervention’s efficacy in real-world care settings, we will also recruit from the Rocky Mountain Cancer Centers (RMCC), the largest community provider of cancer care in Colorado, and DFCI-affiliated regional community oncology practices.

The academic cancer centers, which use the same electronic health record system (e.g., EPIC), will use methods from the pilot study [27] in which they automate identification of patients with advanced ovarian cancer and prescriptions for PARP inhibitors by creating an EPIC workbench or, alternately, obtaining a list of patients treated with PARP inhibitors from the cancer centers’ specialty pharmacists. Trained research assistants (RAs) will review the site’s workbench regularly and Site PIs at Massachusetts General Cancer Center and the Cancer Center at BIDMC will regularly review lists with pharmacists. After receiving permission from patients’ oncologists to approach potentially eligible patients, RAs will contact the patient in person, by telephone, or by secure email to describe the study. If patients are interested, the RA will administer the study eligibility screening. If the patient is eligible and interested, the RA will initiate an oral informed consent process using REDCap’s e-consent framework. After completing informed consent, participants will receive a copy of their completed consent form, asked to complete a baseline survey, and sent a wireless electronic pillbox. If recruitment rates are low at any site, study staff will undergo retraining and approach patients in person – a strategy successfully used during the pilot study.

At the primary community site of RMCC, we will use the triple strategy of practitioner referrals and outreach to potentially eligible patients, direct patient mailings, and onsite flyers—approaches we have used successfully in previous trials with RMCC [25, 35–38]. If needed, we will send an RA onsite to a large RMCC clinic to recruit, a strategy we have piloted but only use as a back-up strategy due to its time and resource demands. Once a potential participant contacts the study team for more information or is referred by a provider, the University of Colorado research team will contact them to share study details and, if interested, complete study eligibility screening. If the person is eligible and interested, the study’s oral informed consent process is initiated with consent documented using REDCap’s e-consent framework. After completion, participants are sent a copy, asked to complete a baseline survey, and provided with a wireless pillbox.

The consent form includes that study participation is entirely voluntary, that participants’ clinical care will not be compromised in any way if they withdraw from the study, and that participants can be removed at the discretion of the principal investigators ([name] and [name]) for reasons such as violating reasonable expectations for study participation.

### Study conditions

#### *REVITALIZE* content and flow

As presented in Table 1, the *REVITALIZE* intervention consists of eight weekly telehealth sessions followed by two telehealth booster sessions at one- and two-month follow-up (e.g., one and two months after the last weekly session). For replicability, each session is guided by a detailed interventionist manual and patient workbook. Weekly *REVITALIZE* sessions focus on patient acquisition of ACT skills and behavior changes tailored to address fatigue in advanced cancer. Specifically, the intervention uses metaphors, structured reflections, and experiential exercises to help patients: (1) acknowledge what they can versus cannot control about fatigue and cancer; (2) mindfully experience and accept fatigue as it shows up here-and-now, which is explored as a less draining alternative to spending significant energy fighting to get rid of it; (3) develop skills for responding to difficult thoughts, beliefs, and images about cancer and fatigue in ways that reduce their influence on well-being and daily behavior; (4) clarify and connect to personal values (what is most important to them); (5) sensitively guide participants to engage in values-based activities and set goals around such activities in a manner appropriate to their energy level; (6) regulate sleep/wake cycles to improve nighttime sleep, including reducing daytime sleep and sleep habits that interfere with nighttime sleep. Booster sessions focus on consolidating and troubleshooting skills and behavior changes to promote enduring benefit. As noted, in response to pilot study participant and interventionist feedback, this content is now covered over eight weekly sessions and two boosters rather than six weekly sessions and one booster (as in the pilot study [27]). However, intervention content remains the same.

**Table 1 Tab1:** Schedule of REVITALIZE study enrollment, intervention, and assessment

	**Pre-randomization (Enrollment)**			**Post-randomization**						
	**Baseline**	**Device Mailing +Set-Up**	**PARPi Device Adherence Data Baseline**	**Intervention Start**	**Mid-point**	**Post- intervention**	**Booster 1**	**Booster 2**	**Primary Endpoint**	**Maintenance Follow-up**
	**Week 0**	**Week 1**	**Weeks 2-3**	**Week 4**	**Week 8**	**Week 13**	**Week 16 **	**Week 20**	**Week 20**	**Week 28**
ENROLLMENT:										
* 1. Eligibility screen*	**X**									
* 2. Informed consent*	**X**									
RANDOMIZATION				**X**						
REVITALIZE (one arm)				**X**	**X**	**X**	**X**	**X**		
ASSESSMENTS (both arms):										
* 1. Patient-Reported Outcomes*	**X**				**X**	**X**			**X**	**X**
* 2. Wisepill device data collection*			**X**	**X**	**X**	**X**	**X**	**X**	**X**	**X**

^**^Timepoints allow ±4 weeks

As in the pilot trial, the *REVITALIZE* intervention will be conducted by secure videoconferencing. Key concepts are communicated using engaging PowerPoint images (see Fig. 1). Parallel images and accompanying home practice worksheets are printed in patient workbooks that are mailed to participants before the intervention begins. If participants lack a home computer/tablet or internet, we loan them a Wi-Fi- enabled tablet and keyboard for use during the study, a process used successfully in another trial in advanced cancer [25].

**Fig. 1 Fig1:**
[figure not shown]
Sample REVITALIZE patient-facing slide

#### Education-enhanced usual care control

EUC participants will receive a printed NCI educational book on cancer survivorship [30] to ensure uniform access to high-quality symptom management and other information across study arms. To ensure similar access to this information in both conditions, this book is sent to all participants, including those in the *REVITALIZE* arm. In addition, EUC participants will have ongoing access to supportive care resources (e.g., social work, psychology, chaplains) available to patients at treating clinics.

Following our published recommendations [39], to account for potential differences in supportive care resources by site, participants in both study arms will report their use of supportive care services used outside of the study (e.g., non-study supportive care use) with a tracker we piloted in a recent trial [36]. We will account for use of non-study supportive care in analyses of outcomes.

#### Intervention training, facilitation, and fidelity

Similar to the *REVITALIZE* pilot, University of Colorado Boulder clinical psychology doctoral students and post-docs who have completed at least one year of training in behavioral therapy will serve as the *REVITALIZE* interventionists. MPIs [name] and [name] provide training in *REVITALIZE* manual content and the ACT approach using experiential role-playing and coaching, evidence-based training approaches [40, 41] used in the pilot and [name]’s other ACT studies [36, 42].

Weekly supervision is provided, and intervention sessions are videotaped for supervision purposes. After each session, study interventionists report on their adherence to the protocolized content for that session using a checklist. Finally, 20% of *REVITALIZE* sessions will be randomly selected for content fidelity ratings by ACT-trained doctoral students or post-docs who are not involved in managing the study.

### Study ethics and integrity

The Dana-Farber Cancer Institute (DFCI) serves as the single IRB for the study. The internal Data Safety and Monitoring Board at DFCI provides additional oversight for data quality, participant safety, and assessment of potential harms. Verbal informed consent is obtained from all study participants, preceded by a verbal discussion of the consent form in person or by phone with a trained study RA to facilitate full understanding prior to signing. At the beginning of the baseline survey in REDCap, participants sign a HIPAA release appropriate to their site to grant permission for the study team to confirm medical eligibility and treatment information in their medical records. Following completion of the baseline survey, the participant is then sent a wireless electronic pillbox (Wisepill) and completes an orientation with a trained study RA, so the participant understands how to use the device. Study coordinators randomize participants using a sequence created by the study biostatistician. The sequence is uploaded into REDCap using the embedded randomization function wherein the sequence is hidden from the study team to reduce potential bias and once assigned cannot be altered. Data confidentiality is ensured by the collection and storage of patient-reported outcome data in REDCap, a HIPAA-compliant system. To reduce potential bias in outcome assessment, REDCap survey links are sent to participants directly. Participant retention and timely data collection are promoted by compensating participants for their time in completing the online assessments. All research team members complete relevant Collaborative Institutional Training Initiative (CITI) training and all university-affiliated members report an annual Disclosure of External Professional Activities (DEPA).

Each study recruitment site completes a site initiation visit prior to onboarding in which study details are presented and discussed. The MPIs have a standing weekly to biweekly meeting and the study coordinators have a standing weekly to biweekly meeting with the MPIs to ensure timely study communication, coordination, and troubleshooting across the administrative sites. Protocol modifications will be submitted for approval to the DFCI IRB and once approved, communicated to the study coordinators at this standing meeting. The senior leadership team (e.g., study Co-Is) meets regularly to review recruitment rates, protocol changes, and study-related updates.

### Patient advisory committee

The study is guided by a patient advisory committee consisting of up to five diverse patients with advanced ovarian cancer who meet quarterly with the study PIs. In the first year, the advisory committee reviewed study materials, surveys, and recruitment strategies to ensure that they were both culturally sensitive and minimally burdensome. In subsequent years, the advisory committee will meet quarterly to review participant recruitment and retention, help with necessary problem-solving throughout the trial, and provide input on study findings, and strategies and networks to disseminate findings.

### Study timeline

As described in *Study Design*, patient-reported primary and secondary outcomes and process variables are assessed at five timepoints: baseline (pre-intervention), mid-intervention (8 weeks after baseline), post-intervention (13 weeks after baseline), and 20- and 28-week follow-up (FU) with 20-week FU serving as the main endpoint and 28-week FU serving to test maintenance or change in effects over a longer time period. After consenting to participate in the study, steps are done in the following sequence, with the next step initiated after the previous one is completed: (1) participants complete the baseline survey; (2) participants begin using the Wisepill wireless adherence tracking devices [33] for 2 weeks to establish a baseline for PARP inhibitor adherence; (3) participants are randomized to condition. Participants will then continue with Wisepill use, their assigned condition, and the study assessments for nearly 7 months.

### Measures

For their time spent completing the surveys in REDCap, as well as to promote participant retention and on-time data collection, participants will receive $20 per survey assessment plus $5 bonus for completion within 48 h of receiving the survey link, for a total of up to $25 per assessment point. The study enrollment, intervention, and assessment timepoints are displayed in Table 1. If participants choose to drop out of the intervention, or develop disease progression during the study but wish to remain in the study, they will retain the option of completing the assessments. In addition, we will compensate participants $25 for returning their supportive care tracking sheet and Wisepill device, for a total of up to $150 per participant across the study.

#### Primary outcome (Aim 1)

The primary outcome of fatigue interference will be assessed using the well-validated 7-item *Fatigue Symptom Inventory (FSI) Fatigue Interference subscale* [28, 29]. Items rated on an 11-point scale (0 = no interference; 10 = extreme interference) assess the extent to which fatigue in the past week interfered with general activity levels, bathing and dressing, work activity (including housework), concentration, relationships, life enjoyment, and mood. This scale has good internal consistency in cancer populations (α = 0.94-0.95) [29] as well as good convergent and discriminant validity and sensitivity to change following intervention [28].

#### Secondary outcomes (Aim 1)

Patient-reported secondary outcomes were tested in the *REVITALIZE* pilot study [27] and reflect measures selected for psychometric strength and brevity, to reduce patient burden. The *PROMIS Cancer Fatigue Short Form*, 7-item measure [43] evaluates fatigue severity [43, 44]. The *Fatigue Self-Efficacy Scale* [45, 46] evaluates people’s belief in their ability to improve their fatigue. The *Fatigue Catastrophizing Scale* [47, 48] assesses catastrophizing about fatigue, and the *Quality of Life*,* Functional Assessment of Cancer Therapy-Ovarian* [49–51] assesses physical, emotional, social/family, and functional well-being.

#### PARP inhibitor adherence assessment (Aim 2)

To assess monthly PARP inhibitor adherence and non-persistence, we will use Wisepill, a simple wireless electronic pillbox monitoring device (4.3”x1.8”x.5”) that sends real-time data to a protected online server when opened. This enables quick identification of any device issues and transmitting full data even if devices are not returned. Wisepill is highly reliable, acceptable, and easy to use [52–55]. It shows similar reliability as MEMS caps [56], greater accuracy than real-time reporting [57], pill counts or self-report [35, 56, 58], and direct association with biologically-measured adherence markers [57]. We used Wisepill to assess anti-cancer medication adherence in prior work [35, 52, 59]. This work established successful procedures for the remote delivery, instructions, and return of Wisepill monitors using post mail that we use in the current study. Study RA’s also complete a phone orientation with each participant to instruct them on how to use the Wisepill and confirm that it is working properly.

Wisepill adherence tracking device data will compute monthly PARP inhibitor adherence as the percent of days per 30-day month that the tracking device is opened once for each dose prescribed that day, divided by 30, using recommended methods for Wisepill data preparation and analysis [53]. PARP inhibitors that are taken once daily will require one Wisepill opening to be considered adherent on that day, whereas PARP inhibitors taken once in AM and once in PM will require two Wisepill openings at separate times to be considered adherent on that day. (As noted above, we stratify by PARP inhibitor regimen to take into account dosing schedules across study arms).

Wisepill-assessed monthly adherence will serve as the main adherence outcome. Wisepill, along with medical chart review, will also assess PARP inhibitor non-persistence, measured as stopping the PARP and not restarting through study end. Finally, medical chart review will be used to evaluate PARP inhibitor dose reductions and interruptions, the latter defined as breaks in PARP inhibitor use that reflect stopping and starting again during the study rather than stopping through study end, and disease progression events.

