### The current study protocol

This protocol describes a two-arm, prospective randomized controlled trial (RCT) to evaluate the efficacy of the *REVITALIZE* intervention in reducing fatigue interference and improving adherence to PARP inhibitors, compared with an education-enhanced usual care condition (EUC). Participants will be patients with advanced ovarian cancer who report moderate to severe fatigue (score of ≥ 4 on the Fatigue Symptom Inventory-3 screen [28, 29]) while on PARP inhibitors. This trial addresses four limitations of prior cancer-related fatigue research by: (1) focusing exclusively on patients with advanced cancer; (2) targeting fatigue associated with a novel precision oncology treatment (PARP inhibitors); (3) primarily targeting fatigue interference, a more realistic main target than fatigue severity among patients with advanced cancer requiring ongoing treatment that causes fatigue; (4) directly testing whether addressing fatigue improves cancer treatment adherence – an underexplored relationship that could inform clinical care.

Comparing *REVITALIZE* to an EUC condition helps to determine if *REVITALIZE* offers benefits beyond those realized by offering standardized cancer survivorship materials developed by the National Cancer Institute [30]. The aims of this study include:

Test the hypothesis that *REVITALIZE*, relative to EUC, will reduce the primary outcome of fatigue interference and reduce fatigue severity and catastrophizing and increase fatigue self-efficacy and quality of life (secondary outcomes).Assess whether *REVITALIZE*, relative to EUC, improves monthly PARP inhibitor adherence, dose interruptions, reductions, and persistence, using wireless medication adherence monitors and medical chart review.Test *REVITALIZE* theory-driven mechanisms of action; specifically, to see if *REVITALIZE* increases acceptance and alignment with values more than EUC, and whether changes in these putative mechanisms predict fatigue-related and quality of life outcomes at follow-up.

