### Data analytic approach

The statistical analysis will be conducted according to the intention-to-treat principle, with all randomized participants included in the primary analyses. Descriptive statistics will be used to evaluate baseline and follow-up outcome measures, including assessment of distributions, potential outliers, and patterns of missing data. For continuous outcomes, we will summarize mean changes from baseline with corresponding 95% confidence intervals (CIs) at each follow-up time point for both groups (Enhanced Usual Care vs. *REVITALIZE*). For binary outcomes (e.g., presence of PARP inhibitor dose delays, interruptions, or discontinuation), we will estimate proportions with corresponding 95% CIs. If clinically meaningful imbalances are observed between groups, adjusted analyses using regression or stratified models will be performed.

For Aim 1, the primary analysis of change in fatigue interference at week 20 will tested using a a two-sample t test (without covariate adjustment). As a secondary analysis, linear regression (ANCOVA) of the outcome on the intervention indicator, adjusting for the baseline value of the outcome and prespecified baseline variables (race/ethnicity, education, age, and income) will be used. If any baseline variable shows imbalance (standardized mean difference > 0.10), it will be retained in the regression model; otherwise only the baseline value of the outcome will be included alongside the variable for condition. Longitudinal mixed-effects models will be conducted as additional secondary and sensitivity analyses. Aim 2 adherence outcomes will be assessed using mixed-effects models for Wisepill data and logistic regression for binary adherence indicators. Aim 3 will evaluate whether the conditions differ on change over time in the hypothesized process variables for *REVITALIZE—* acceptance and values alignment. In addition, we will test mediation of intervention effects on fatigue interference through acceptance and values alignment using the linear regression mediation framework outlined below as well as the multiple mediation framework of Preacher and Hayes [62], with sensitivity analyses using structural equation models.

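### PARP inhibitor non-persistence counts every permanent stop, including stops at disease progression, which pulls the Aim 2 persistence comparison towards no difference if such stops are similar in the two arms

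*Protocol article*

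**What the plan says.** In the protocol article, the section on PARP inhibitor adherence assessment (Aim 2) defines non-persistence, from Wisepill data and chart review, as "measured as stopping the PARP and not restarting through study end". No reason for stopping is required and none is excluded. The same paragraph distinguishes interruptions from permanent stops and adds "and disease progression events" to the items abstracted from the chart. It does not say how these events bear on persistence.

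The Data analytic approach follows the intention-to-treat principle, "with all randomized participants included in the primary analyses". It treats discontinuation as a simple binary outcome ("presence of PARP inhibitor dose delays, interruptions, or discontinuation), we will estimate proportions with corresponding 95% CIs") and plans "logistic regression for binary adherence indicators". It mentions no split by reason and no competing event.

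On progression, the Measures section says that participants who "develop disease progression during the study but wish to remain in the study, they will retain the option of completing the assessments". The Aim 2 question appears under The current study protocol, which lists among the trial's contributions "directly testing whether addressing fatigue improves cancer treatment adherence".

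**The concern.** Aim 2 asks whether helping patients cope with fatigue keeps them on their drug. REVITALIZE works through acceptance, values-based activity and sleep regulation, and nothing in the article claims an effect on the tumour. The Background calls advanced disease typically incurable, and eligibility includes maintenance after platinum-sensitive recurrence, so some participants may progress and stop within the nearly 7 months of follow-up. Under the stated definition each of these stops is a failure to persist.

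If such stops fall about equally in both arms, they add events unrelated to the intervention and move the comparison towards no difference. A null persistence result would be harder to interpret. A chance imbalance in progression could also look like an effect on persistence.

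**Working it through.** **Inputs from the article.** Power and sample size estimation gives 96 evaluable participants per arm, a two-sided alpha of 0.05, and for the chart-review outcomes 80% power at Cohen's h = 0.4 and 93% at h = 0.5.

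**The plan's own figure.** With the arcsine approximation, power = Φ(h·√(96/2) − 1.96):
- h = 0.4: Φ(0.4 × 6.928 − 1.96) = Φ(0.81) = 79%
- h = 0.5: Φ(0.5 × 6.928 − 1.96) = Φ(1.50) = 93%

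Both agree with the stated values. The article names Fisher's exact test, which gives lower power: about 70% to 75% at h = 0.4 for control rates between 15% and 50%. The arcsine formula is kept below because it reproduces the plan.

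**Dilution.** Let p be the probability of a permanent stop for a reason other than progression, and q the probability of a progression stop, equal in both arms. Then all-cause stop = q + (1 − q)p. The risk difference shrinks by the factor (1 − q), and h = 2·arcsin√p₁ − 2·arcsin√p₂ is recomputed from the all-cause rates.

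The article gives no stop or progression rates, so every rate here is an assumption. For other stops of 15% (control) and 5% (REVITALIZE):

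| q | Control | REVITALIZE | Risk difference | Risk ratio | h | Power |
|---|---|---|---|---|---|---|
| 0 | 15.0% | 5.0% | 10.0 points | 0.33 | 0.34 | 66% |
| 5% | 19.25% | 9.75% | 9.5 points | 0.51 | 0.27 | 47% |
| 10% | 23.5% | 14.5% | 9.0 points | 0.62 | 0.23 | 36% |
| 15% | 27.75% | 19.25% | 8.5 points | 0.69 | 0.20 | 29% |
| 20% | 32.0% | 24.0% | 8.0 points | 0.75 | 0.18 | 23% |

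Example at q = 15%: 0.15 + 0.85 × 0.15 = 0.2775 and 0.15 + 0.85 × 0.05 = 0.1925. The ratio is 0.69, h is 0.20, and power = Φ(0.201 × 6.928 − 1.96) = 29%.

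**Starting from the plan's h = 0.4 instead.** If that effect is taken to apply to stops other than progression, power starts at 79% and becomes:

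| Other stops, control vs REVITALIZE | q = 5% | q = 10% | q = 20% |
|---|---|---|---|
| 15% vs 3.9% | 58% | 44% | 28% |
| 20% vs 6.8% | 64% | 52% | 36% |
| 30% vs 13.7% | 70% | 61% | 46% |

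**Counting only other stops, with progression as a competing event.** The arm proportions become (1 − q)p, so the risk ratio stays at its undiluted value. For 20% vs 6.8%, power is 77%, 74% and 68% at q = 5%, 10% and 20%, against 64%, 52% and 36% under the all-cause definition. Losing the progression stops from the count costs less than keeping them in.

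**The case against.** All-cause stopping is a legitimate outcome. It is objective, needs no attribution of cause and fits the intention-to-treat principle. This stands, and the all-cause result should be kept.

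Progression occurs after randomization. If REVITALIZE improves adherence, progression may not be independent of arm, and removing progression stops could remove part of a real effect. Equal rates are an assumption. This stands as a limit on the cause-specific analysis and is the reason to report both.

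Eligibility requires at least 2 months already on the drug, ECOG 0 to 2 and at least 8 months' anticipated treatment, longer than the study. This lowers q but does not bring it to zero, because it is an expectation at consent. A reader might take the Measures clause on progression to show that many progressions are expected. It is only a contingency provision about completing assessments.

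A reader might also infer that the stated Aim 2 power is wrong. The article does not support that: h = 0.4 is not tied to stops other than progression, and if it refers to the outcome as defined, there is no shortfall against the stated figure. Nor would a null result be impossible to interpret, because the abstracted progression events allow a partial split afterwards. Such a split would be post hoc and would infer the reason from timing.

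Finally, the unseen full protocol or analysis plan may classify stops by reason. But the definition the article fixes is explicit and covers every permanent stop, so a different primary handling would depart from it.

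**Conclusion.** The point holds as a weakness in a stated outcome definition. Followed as written, non-persistence mixes stops the intervention might influence with stops at progression that it is not designed to influence, and the progression data collected alongside play no stated part.

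The direction follows if progression stops are similar in the two arms. The size cannot be fixed from the article: the illustrative range in the table rests wholly on assumed rates, and the 8-month eligibility criterion points to its lower end. On the absolute scale the change is modest, from 10 points to between 9.5 and 8.

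The stakes are limited. Monthly Wisepill adherence is the main adherence outcome and fatigue interference is the trial's primary outcome, so no primary conclusion depends on this. Persistence is nonetheless named in Aim 2, and the change is cheap enough to be worth making.

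**What to change.** In the existing chart abstraction, record a reason for each permanent stop (disease progression, death, planned completion, other), assigned blind to arm. Prespecify a persistence analysis of stops for other reasons, with progression, death and planned completion as competing events, using cumulative incidence or cause-specific hazards by arm from randomization. Report it beside the all-cause result, and show progression stops by arm. Settle this before outcomes are compared between arms.

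The cost is one field on a chart review already planned and a change to the outcome wording. There are fewer counted events, and assigning reasons takes some judgement that blinding the abstractor does not wholly protect, since patients know their arm. The remaining category still mixes fatigue with other reasons for stopping. The change concerns measurement and analysis only, not when treatment is stopped.
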